Mifepristone (11-[4-(Dimethylamino)phenyl]-17-hydroxy-17-[1-propynyl]-[11ß,17ß]-estra-4,9-dien-3-one), a derivative of the synthetic progestin norethindrone, is a potent competitive glucocorticoid and progesterone receptor antagonist, also known as RU 486 31. Mifepristone has approximately three-fold higher affinity for the glucocorticoid receptor than dexamethasone, and 18-fold the affinity of cortisol 32. Mifepristone causes glucocorticoid antagonism by reducing translocation of the receptor to the nucleus and also by antagonising glucocorticoid-dependent transcriptional activity 33. Mifepristone is well absorbed and following oral ingestion has a bioavailability of more than 30%, and peak serum levels are reached within 1-2 hours, with a half-life of 24-48 hours 34. In man administration of mifepristone >200mg/day blocks central and peripheral glucocorticoid action, with resultant activation of the HPA axis: in normal volunteers 200 mg/day of mifepristone for eight days increased plasma, salivary, and urinary cortisol levels secondary to a slight rise in plasma ACTH, but without clinical or biological evidence of cortisol deprivation 35. Thus, these biochemical assessments allow confirmation of blockade of glucocorticoid action. On longer-term treatment, symptoms of adrenal insufficiency are possible, and highlight the need of clinical assessment, as the usual biochemical parameters of cortisol and ACTH levels cannot be reliably interpreted to assess this. Mifepristone-induced adrenal insufficiency can, however, be overcome: administration of dexamethasone 1mg is sufficient to overcome the effects of mifepristone 400mg 32. The efficacy of mifepristone has also been assessed in few patients with severe Cushing’s syndrome. Following the original description in 1985 36 a total of 18 patients in the world literature in whom this drug has been used for this purpose have been described to 2007 37. It has been found to be effective in patients with excess cortisol from adrenal tumours or the ectopic ACTH syndrome, and in reducing clinical parameters including hypertension, glucose homeostasis and psychosis. A study in severe ectopic ACTH syndrome is currently recruiting, with a starting dose of 600mg/day, titrating up to 20mg/kg/day. In addition to the anti-glucocorticoid effects, the anti-progestogenic effects appear at lower doses. The anti-progestogenic effects have also been exploited in the long-term treatment of patients with meningiomas, breast cancer (200-400mg/day) and myomas, with a good safety record (up to 14 years of treatment for meningiomas, mifepristone 200mg/day) 38,39. The anti-progestogenic effects of mifepristone have been also been shown to cause reversible endometrial hyperplasia after six months of therapy 40. Mifepristone is currently licensed at single doses of 600mg to induce medical termination of pregnancy, without evidence of adrenal insufficiency.

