***Inclusion criteria*** Patients will be eligible for inclusion if: they are males and over 18, or postmenopausal women; have an adrenal incidentaloma with benign characteristics diagnosed on CT or MRI; lack clinical features classically associated with Cushing’s syndrome; have evidence of excess cortisol as shown by lack of suppression of serum cortisol on 1mg over-night dexamethasone suppression or 2mg /day 48 hour low-dose dexamethasone suppression testing 41; stable antihypertensive and diabetic medication for two months prior to study entry.

***Exclusion criteria*** will include: evidence of local or systemic malignancy; overt Cushing’s syndrome; severe uncontrolled diabetes mellitus or hypertension; pregnancy; clinically significantly impaired cardiovascular function (e.g. stage IV cardiac failure); severe liver disease (liver enzymes ≥ 3 x the institutional upper limit of normal range); significantly impaired renal function (eGFR <30/min); uncontrolled severe active infection; treatment with approved or experimental steroidogenesis inhibitors, adrenolytic agents, within four weeks of admission; In women, known endometrial cancer, history of endometrial hyperplasia or vaginal bleeding of unknown cause; requirement for inhaled or systemic glucocorticoids for existing disease; impaired mental capacity or markedly abnormal psychiatric evaluation that precludes informed consent.

***Justification of period of study****:* The choice of eight weeks reflects the desire to allow sufficient period for the cardiovascular and metabolic effects of glucocorticoid antagonism to become manifest, and is extrapolated from the effects seen in the few patients with Cushing’s syndrome treated with mifepristone 37.

***Justification of dose and dose interval****:* The dose of 200mg twice daily has been chosen to provide partial blockade of glucocorticoid receptor activity. The interval is twice daily based on the known half-life of the drug and the wish to *partially* block glucocorticoid activity over the 24-hour period, without overt glucocorticoid deficiency, and to minimize the possibility of a rebound effect of increased cortisol exposure at the end of the dose interval, as may happen by using a single dose of mifepristone 400mg/24 hours.

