***Drug administration and compliance****:* A check on the blister packs of the tablets issued and therapeutic drug monitoring will be performed at each visit to assess and encourage compliance. All existing medication will be left unaltered for the duration of the study. The first dose of the drug (Treatment start) will be given at Visit 2 (week 0) after baseline tests have been performed. The last dose (Treatment end) will be taken in the morning at Visit 8 (week 8). The drug will be administered 1 hour before food to maximise bioavailability as mifepristone is absorbed rapidly.

***Safety****:* Clinical assessment by BP, P, temperature, weight and questioning for fatigue, headache, anorexia, nausea, arthralgia, myalgia, and abdominal pain (potential glucocorticoid deficiency, a predictable effect of mifepristone based on its known action) will be made at each study visit. Clinical experience is, however, that even total adrenal insufficiency is well tolerated in the absence of physical or infective stressors. For safety purposes each patient will also be issued with written instructions which will tell them what to do if this side effect occurs and with a supply of two dexamethasone 1mg tablets (sufficient to overcome the effects of mifepristone 400mg by taking dexamethasone 1mg/day for 2 days) to be taken on the advice of the investigators if significant symptoms are reported. In such circumstances any study subject will be asked to attend the CRF either that day or the next working day, and data entered into the CRF accordingly, and the subject asked to stop the mifepristone and withdrawn. Other uncommon but documented side effects of mifepristone used at this dose and for this time period include: skin rash (maculopapular), increased eosinophil count, joint pain, hypokalaemia. When used for >3-6 months duration endometrial hyperplasia, uterine fibroma, and endometriosis are described.

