**8.0 Ethical issues**

The study will be approved by the appropriate NHD Research Ethics Committees prior to commencement of the study. The study will be performed in accordance to the Declaration of Helsinki, ICH guidelines covering Good Clinical (research) Practice and the European Clinical Trials Directive and NHS Research Governance. A steering committee will be created according to GCP guidance. [name] (Sheffield) has already agreed to undertake this. Any adverse event will be flagged. An adverse event (AE) can be any unfavourable and unintended sign (including an abnormal laboratory finding), symptom, or disease temporally associated with the use of a medicinal product, whether or not considered related to the medicinal product.

If depression questionnaire highlights a level of depression requiring medical or psychiatric intervention necessary action will be taken by research team members.

Previous data suggests that mifepristone is well tolerated when taken for long periods of time (months to years). The main concern is the potential for inducing adrenal insufficiency.

*Safety and well-being of study participants*

Patients will be monitored for the non-specific symptoms and signs of relative adrenal insufficiency. It is unlikely that there will be any unanticipated side effects, but any potential adverse event will be recorded according to GCP guidelines and standard definitions.

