##### *Safety assessments*

##### Safety assessments will consist of monitoring and recording of all non-serious and serious adverse events and regular monitoring of blood chemistry, regular measurement of vital signs, and performing of physical examination and body weight estimation. Patients will be monitored for signs of adrenal insufficiency and will be educated on how to manage adrenal insufficiency and will carry a steroid card and will have a supply of 1mg oral dexamethasone to use in the event of symptoms (see above 2.3). A safety sheet assessment will be filled in at each visit by the investigator whilst on treatment.

Safety population – all patients who received at least one dose of Mifepristone will be considered for the safety evaluation.

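### The protocol's reassurance about adrenal insufficiency assumes no physical or infective stressor, but no rule defers booked major surgery or requires mifepristone to be stopped and steroid cover given before symptoms appear

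*Protocol*

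**What the plan says.** Section 5.2 (Safety) treats glucocorticoid deficiency as a predictable effect of mifepristone and adds that, in clinical experience, "even total adrenal insufficiency is well tolerated in the absence of physical or infective stressors". Section 8.0 says: "The main concern is the potential for inducing adrenal insufficiency". Section 4 accepts the same risk: "On longer-term treatment, symptoms of adrenal insufficiency are possible". It adds that cortisol and ACTH cannot be relied on to detect insufficiency while the drug is taken, so detection is clinical.

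The exclusion criteria in section 5.2 contain one item aimed at a stressor, "uncontrolled severe active infection". No item covers planned surgery or another physical stressor.

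The rescue arrangements are these:

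- Section 5.2 (Safety): each patient receives "written instructions which will tell them what to do if this side effect occurs" and two 1 mg dexamethasone tablets, "to be taken on the advice of the investigators if significant symptoms are reported". A patient with such symptoms is seen that day or the next working day, stops mifepristone and is withdrawn.
- Section 8.0 (Safety assessments): patients are given teaching on handling this complication. They also "will carry a steroid card and will have a supply of 1mg oral dexamethasone to use in the event of symptoms".
- Section 8.0 (Definition of Hospitalisation): admission for elective surgery that does not result from an adverse event need not be counted as one. Nothing is said there about study drug or steroid cover.

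**The concern.** The reassurance is conditional, and an operation is a plain case of the condition failing. A booked operation can also be known before the first dose, so it can be handled at entry. As written, a patient with major elective surgery already scheduled meets the listed criteria. No section then says what to do with mifepristone beforehand.

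A trigger based on reported symptoms suits this situation poorly. The monitored complaints include fatigue, headache, nausea and abdominal pain. A patient under anaesthesia cannot report them, and they are hard to interpret after an operation. That is a clinical inference; the protocol does not say it.

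What is at stake is the safety of the individual patient. No weight is put on any effect on the endpoints.

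**Working it through.** **Side-by-side check.** The protocol gives no figure of its own on this point, so the test is whether any section covers a foreseeable stressor before symptoms occur.

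| Place in the protocol | What it does | Bars booked surgery? | Requires stop and cover before symptoms? |
|---|---|---|---|
| 5.2, exclusion criteria | Excludes serious uncontrolled infection; the list is introduced as inclusive, so not closed | No | No |
| 5.2, dose justification | Aims at partial blockade, "without overt glucocorticoid deficiency" | No | No |
| 5.2, visit schedule | Weekly to week 4, then at weeks 6 and 8 | No | No |
| 5.2, Safety | Instructions, dexamethasone, urgent review, withdrawal | No | No; starts with symptoms |
| 8.0, Safety assessments | Education, steroid card, dexamethasone | No | No; education and card act in advance but set no stop rule |
| 8.0, Concomitant therapy | New medication needs the investigator's prior consent | No | No; may bring surgery to notice |
| 8.0, discontinuation | Lists ten reasons; surgery and intercurrent stress are not named | No | No |
| 8.0, hospitalisation | Elective surgery as a reporting matter | No | No |

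**How far the supporting evidence reaches.** Section 4 cites a volunteer study of 200 mg/day for eight days without evidence of cortisol deprivation. This trial gives 2 × 200 = 400 mg/day for 56 days: 400/200 = 2 times the daily dose and 56/8 = 7 times the duration. Section 4 also cites single 600 mg doses without adrenal insufficiency, and long-term use with a good safety record, including 200–400 mg/day in breast cancer, which does reach this trial's dose. None of this evidence is described as covering operations.

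**Exposure window.** Section 4 gives a half-life of 24–48 hours. Taking five half-lives as clearance (an assumption):

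- 5 × 24 h = 5 days; 5 × 48 h = 10 days.
- Window = 56 + 5 = 61 days to 56 + 10 = 66 days.
- At the follow-up visit, 72 hours after the last dose, the fraction of drug remaining is 0.5^(72/24) = 0.125 to 0.5^(72/48) = 0.35.

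This is a planning window based on drug remaining. It does not measure receptor blockade or clinical risk.

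**Chance that it arises.** The protocol gives no rate of major elective surgery, so three rates are assumed. With six patients, P(at least one operation) = 1 − exp(−6 × rate × days/365).

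| Assumed rate per patient-year | 61 days | 66 days |
|---|---|---|
| 0.01 | 0.010 | 0.011 |
| 0.05 | 0.049 | 0.053 |
| 0.10 | 0.095 | 0.103 |

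For example, at 0.05 and 66 days: 6 × 0.05 × 66/365 = 0.0542, and 1 − exp(−0.0542) = 0.053. The calculation counts every major elective operation in the window. Those already booked at entry are a subset. It leaves out emergency surgery, trauma and infection.

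**The case against.** The strongest reply is that nothing in the protocol is misstated. The sentence on tolerance is a general clinical remark with a correct qualifier, and the plan does not rest on it: instructions, dexamethasone, urgent review and withdrawal follow at once. Temperature and symptoms are checked at every visit.

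The requirement for prior consent to new medication matters too. Anaesthetic and peri-operative drugs are new medication, so a planned operation should normally reach the investigator beforehand. The steroid card would alert a surgical team. The exclusion list leaves the investigator room to defer such a patient, and the instruction sheet, which is not shown, may say more about operations.

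All of this stands as mitigation. It defeats a stronger reading that a reader might be tempted to draw, namely that the plan has no advance safeguard and would knowingly dose patients through surgery. The documents do not support that. What survives is narrower. Each safeguard makes it likelier that someone notices, but none tells the investigator to defer the patient, stop the drug or arrange cover before symptoms. The protocol describes the instruction sheet in terms of what to do once the side effect occurs.

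It is also fair to object that a remedy confined to surgery would leave infection and trauma open, since the quoted condition covers both. The fix therefore includes them.

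**Conclusion.** The point holds as a minor gap in the eligibility and safety rules. The condition on the reassurance is secured only for severe infection at entry, and the response to any later stressor waits for symptoms. Likelihood is low: about 1% to 10% that any of the six patients has a major elective operation in the window, over the assumed rates.

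Two inferences should not be drawn. The percentages are not a risk of adrenal crisis or of harm. They describe opportunity only, rest on assumed rates, include operations not yet booked at entry, and take no account of consent, the steroid card or deferral. Nor does the protocol's reversal figure (dexamethasone 1 mg against mifepristone 400 mg, sections 4 and 5.2) show that 1 mg is adequate cover for an operation; the documents offer it only as reversal of the drug's effect.

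The conclusion depends on the protocol text alone and would weaken if the patient instruction sheet already covers operations and acute illness.

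**What to change.** 1. Add to the exclusion criteria in section 5.2: elective surgery under general or regional anaesthesia (minor procedures excepted) scheduled from Visit 2 until about 10 days after the last dose; entry may be deferred until after recovery. Check at Visit 1 and again at Visit 2 before the first dose. The 10 days are five half-lives at the upper limit in section 4, which is an assumption.

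2. Add to section 5.2 (Safety): newly planned or emergency surgery, significant trauma or significant infection in this period is notified to the investigator at once; mifepristone is stopped; and glucocorticoid cover is arranged without waiting for symptoms. The endocrinologist and treating team set the dose, which is not taken from the 1 mg reversal figure. Such patients follow the discontinuation rules in section 8.0.

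3. Put the same rule in the patient instructions, because most of the 10-day tail falls after the 72-hour follow-up visit.

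The cost is one question asked twice, one criterion and a short safety rule. The downside is an occasional deferred or withdrawn patient. Withdrawal matters more with six patients, but deferral is easy: section 5.7 reports 50 patients meeting the entry criteria, and section 8.0 (consent) says the intervention needs no particular time window.

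### Section 5.2 supplies 48 hours of dexamethasone rescue but lets the visit wait until the next working day, so the tablets can run out first over a weekend or an adjoining holiday

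*Protocol*

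**What the plan says.** The Safety paragraph of Protocol Section 5.2 sets out the rescue arrangements for suspected glucocorticoid deficiency. Each patient is issued "with a supply of two dexamethasone 1mg tablets (sufficient to overcome the effects of mifepristone 400mg by taking dexamethasone 1mg/day for 2 days". The tablets are "to be taken on the advice of the investigators if significant symptoms are reported". In that event "any study subject will be asked to attend the CRF either that day or the next working day", with "the subject asked to stop the mifepristone and withdrawn". The paragraph does not say whether mifepristone stops when symptoms are reported or at the visit.

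The later text headed Safety assessments, in Section 8, mentions the supply again but gives no quantity. No section provides further tablets, a maximum interval in hours before the visit, or a rule for weekends and holidays.

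On the importance of the risk, Section 8.0 says "The main concern is the potential for inducing adrenal insufficiency". The Background (Section 4) says "On longer-term treatment, symptoms of adrenal insufficiency are possible, and highlight the need of clinical assessment", and explains that cortisol and ACTH cannot be relied on to judge adrenal insufficiency in a patient taking mifepristone. Section 5.2 also records the view that "even total adrenal insufficiency is well tolerated in the absence of physical or infective stressors".

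**The concern.** Two rules in one paragraph are set on different clocks. The tablet supply is fixed in hours (48). The latest permitted visit is fixed in working days, which can be a much longer interval. A patient and an investigator can both follow the protocol and still reach a point where the tablets are finished and nobody has examined the patient.

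This matters because the Background makes clinical assessment the way to judge adrenal insufficiency on this drug, so it is sensible for rescue to last until that assessment. It is also the adverse effect that the protocol ranks first. The point concerns safety operations. It does not affect any estimate or test.

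**Working it through.** **Inputs from the Protocol**
- Supply: 2 tablets of 1 mg, taken at 1 mg/day (Section 5.2, Safety).
- Latest visit: the working day after the report (Section 5.2, Safety).
- Mifepristone 200 mg twice daily (Sections 5.2 and 5.8), half-life 24-48 h (Section 4).

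**Assumptions, not in the Protocol**
- Monday to Friday working week.
- First rescue tablet at 0900h or 1800h.
- Visit between 0900h and 1700h.
- Each tablet covers 24 h.
- The patient is not seen on the day of the report.

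**Step 1: the plan's own figure.** Cover = tablets x strength / daily dose = 2 x 1 mg / (1 mg/day) = 2 days = 48 h. This reproduces the two days stated in Section 5.2.

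**Step 2: time from first tablet to visit.** For a visit d calendar days later, the shortest interval (1800h start, 0900h visit) is 24d - 9 h. The longest (0900h start, 1700h visit) is 24d + 8 h. Uncovered time = interval - 48 h. Tablets needed = interval / 24, rounded up.

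| Start and latest permitted visit | d | Interval (h) | Uncovered (h) | Tablets needed |
|---|---|---|---|---|
| Mon-Thu, ordinary week, to next day | 1 | 15-32 | none | 1-2 |
| Sat to Mon, or across a single midweek holiday | 2 | 39-56 | 0-8 | 2-3 |
| Fri to Mon, ordinary weekend | 3 | 63-80 | 15-32 | 3-4 |
| Fri to Tue (Monday holiday), or Thu to Mon (Friday holiday) | 4 | 87-104 | 39-56 | 4-5 |
| Thu to Tue, four-day holiday weekend | 5 | 111-128 | 63-80 | 5-6 |

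The Friday-to-Monday gap remains even for an evening start and the earliest Monday slot (63 - 48 = 15 h).

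**Step 3: drug remaining when the tablets end.** If mifepristone stops with the first rescue tablet, the share left after t hours is 0.5^(t / half-life). At 48 h this is 25% (half-life 24 h) to 50% (half-life 48 h). At 63 h it is 16% to 40%. Some blockade can therefore outlast the supply.

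**Step 4: is that amount large?** The calculation assumes linear kinetics at steady state and ignores bioavailability on both sides.
- Trial regimen: the amount just after a dose is 200 / (1 - 2^(-12/half-life)) = 683 mg (24 h) or 1,257 mg (48 h). After 48 h this falls to 683 x 0.25 = 171 mg, or 1,257 x 0.5 = 629 mg.
- Volunteer regimen in Section 4 (200 mg/day, no evidence of cortisol deprivation): the peak is 200 / (1 - 2^(-24/half-life)) = 400 or 683 mg, and the trough is 200 less, i.e. 200 or 483 mg.

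When the tablets end, the remaining drug is below the volunteer trough (171 against 200 mg) or between trough and peak (629 against 483-683 mg). It does not exceed the volunteer range.

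**The case against.** The strongest defence has four parts.

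- **The tablets are sized to the drug.** The protocol never says that they must last until the visit; it justifies them as enough to overcome 400 mg of mifepristone. This stands, in that the two rules do not contradict each other. The step from clinical assessment being needed to rescue lasting until that assessment is an inference, though a modest one.
- **An investigator is already involved.** Rescue starts on medical advice, the same-day option closes the gap, and patients receive written instructions, a steroid card and education. The written instructions are not at hand and may deal with running out. This lowers the risk, but the later visit remains expressly permitted and no further supply is stated.
- **The clinical consequence may be small.** The dose aims at partial blockade, Section 5.2 regards adrenal insufficiency as well tolerated without stressors, and Step 4 gives no sign of unusual residual exposure. This stands, with two limits. The comparison is with normal volunteers, whereas Section 4 describes partial suppression of the adrenal axis in these patients. A patient who has not been seen is also one in whom stressors have not been excluded.
- **The clock times are assumed.** Section 5.8 gives 0900h for scheduled visits only; nothing fixes the hour of a rescue visit. A 0700h Friday report seen on Monday at 0900h is a 74 h wait, so starts outside the assumed hours also count.

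From this last point, a reader might infer that the gap is confined to one fixed window or share of the week. The documents set neither visit hours nor working hours for rescue, so they do not support such a figure.

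A reader might also take the Section 8 wording, "will have a supply of 1mg oral dexamethasone to use in the event of symptoms (see above 2.3", as a conflicting trigger for self-treatment. It is shorthand that points back to fuller text, and its outdated section number is clerical.

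**Conclusion.** The point holds as a minor gap in the safety provisions. Under the later of the two permitted visit times, 48 h of rescue does not reach a Monday visit after a Friday start. It falls further short when a public holiday adjoins the weekend. A Saturday start or a single midweek holiday gives a small shortfall or none.

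The direction of the Friday result does not depend on the start and visit times tried; the exact hours do. With project start in November 2008 and the last visit in May 2009 (Section 5.10), the holiday cases are realistic.

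A reader might infer that patients would be left in danger or that the 1 mg/day rescue dose is inadequate. The documents support neither. Harm is not shown, and nothing here questions the dose.

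**What to change.** In the Safety paragraph of Section 5.2, do one of the following:

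- Issue enough 1 mg dexamethasone tablets to last until the latest permitted visit, labelled 1 mg/day until seen. Four tablets (96 h) cover an ordinary weekend (at most 80 h). Six (144 h) also cover a four-day holiday weekend (at most 128 h).
- Keep two tablets and require same-day attendance whenever the next-working-day visit would be more than 48 h after the first tablet.

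In either case, state that mifepristone stops when the first rescue tablet is taken, and match the patient instructions.

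The first option costs 2 extra tablets x 6 patients = 12, or 4 x 6 = 24. Its downside is slightly more unsupervised dexamethasone, up to 4-6 mg in place of 2 mg. The second adds no dexamethasone but needs a place to be seen on non-working days, for example on the Saturday before a Monday holiday. Either is a change of a sentence or two, best made before the first dose.
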